### Measurement items and procedure

2.10

Several relevant examinations will be conducted before the baseline, at the baseline, at week 4, 12, and 24 during treatment. General information will be collected, including the name, age, sex, height, weight, contact information, physical examination, laboratory examination results, and history of present illness, other diseases, personal life, menstruation, marital and fertile, allergy, and family members.

### Primary outcome

2.11

The primary outcome is the eGFR value, and it is calculated using the CKD-EPI creatinine equation, to evaluate the kidney function before and after the intervention on visit 1 to 4 (listed in Table 3).

**Table 3 tbl3:** The measurement items and study procedure.

Items	Screening	Treatment			
Timepoint	V0(-1 weeks)	V1(0 week)	V2(4 weeks)	V3(12 weeks)	V4(24 weeks)
Informed consent	X				
Inclusion/exclusion criteria	X				
Demographic data	X				
Medical history	Χ				
Drug combination	Χ	Χ	Χ	Χ	Χ
Randomization		Χ			
Allocation		Χ			
Physical examination	Χ	Χ	Χ	Χ	Χ
TCM symptoms	Χ	Χ	Χ	Χ	Χ
Kidney function (eGFR, Scr, BUN, SUA)	Χ	Χ	Χ	Χ	Χ
Serum electrolytes	Χ	Χ		Χ	Χ
24-h urine test	Χ	Χ		Χ	Χ
UACR	Χ	Χ		Χ	Χ
Renal tube function	Χ	Χ		Χ	Χ
Inflammatory mediators		Χ		Χ	Χ
Renal ultrasound	Χ	Χ			Χ
Blood, urine and stool routine	Χ	Χ		Χ	Χ
Hepatic function	Χ	Χ		Χ	Χ
Electrocardiogram	Χ	Χ		Χ	Χ
Adverse events			Χ	Χ	Χ
Drug distribution		Χ	Χ	Χ	
Drug collection			Χ	Χ	Χ

X indicates that data need to be collected during the visit.

TCM, traditional Chinese medicine; eGFR, estimated glomerular filtration rate; Scr, serum creatinine; BUN, blood urea nitrogen; SUA, serum uric acid; UACR, urine microalbumin to creatinine ratio.

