### Sample size

2.5

The sample size is issued from the primary outcome that is an alteration in baseline estimated glomerular filtration rate (eGFR). According to a previous report [8], the average eGFR value of the control group is estimated to be 34.7 mL/min/1.73 m^2^. After treatment with JNSF, the value for the intervention group could be increased by 10 mL/min/1.73 m^2^, and its standard deviation would be approximately 18.1 mL/min/1.73 m^2^. If we set the type 1 risk level at 5% and the power at 80%, we calculated that the minimum sample size for each group is 53 participants, using the formula: $t=\frac{\bar{x_{1}}-\bar{x_{2}}}{\sqrt{\frac{\left(n_{1}-1\right)s_{1}^{2}+\left(n_{2}-1\right)s_{2}^{2}}{n_{1}+n_{2}-2}\left(\frac{1}{n_{1}}+\frac{1}{n_{2}}\right)}}$. Assuming a drop-out rate of approximately 10%, we determined that the sample size should be increased to 59 in both groups, to include a total of 118 patients.

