### Randomization procedures

2.6

Potential participants will be screened for eligibility a week anterior to study randomization. Participants will be randomly assigned as a consequence of a randomization schedule to receive JNSF treatment coupled with febuxostat (intervention group) or JNSF placebo treatment coupled with febuxostat (control group).

These treatments are changed into two groups A and B by the independent statistician. A random numbering (1:1) is formulated based on complete randomization with a block size of 4 via SPSS software.

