#### Diagnostic criteria for patients with stages 3–4 of CKD

2.8.2

Recruited male and female patients should exhibit abnormal laboratory test results or anomalies of renal structure and a loss of endocrine function beyond three months. Patients should be diagnosed with an eGFR value ≥ 15 mL/min/1.73 m^2^ and <60 mL/min/1.73 m^2^. The eGFR should be computed utilizing the chronic kidney disease epidemiology collaboration (CKD-EPI) creatinine equation.

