**Exclusion criteria**
Patients are to be unentitled for participation if:
◆ The patient is probably or distinctly possible or definitely allergic to any of the components of the intervention or control drugs
◆ 24-h proteinuria value > 1 g
◆ The patient is diabetic
◆ The patient has had unresolved acute kidney injury, nephrotic syndrome, inherited kidney diseases, another serious disease, or renal transplantation in the previous 3 months
◆ The patient disagrees to engage in the study
◆ The patient has chronic hepatitis, or hepatic dysfunction induced by drug or other pathogens
◆ The patient has recently participated in another clinical trial
◆ The patient is taking medications as similar with JNSF
◆ The patient has a complication or history of malignant tumors, while made an exception for that the malignant tumor is untreated and not recurred within 5 years

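### Change in eGFR rests on the single V1 value although a second pre-dose eGFR is scheduled at V0; averaging the two is an optional precision gain that needs no extra visit

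*Protocol article*

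**What the plan says.** Section 2.10 gives the timetable: "Several relevant examinations will be conducted before the baseline, at the baseline, at week 4, 12, and 24 during treatment". This separates a pre-baseline visit from the baseline visit. In Table 3 they are V0 (week -1, screening) and V1 (week 0, with randomization, allocation and first drug distribution).

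Table 3 marks the row "Kidney function (eGFR, Scr, BUN, SUA") at all five visits. The rows for the 24-h urine test, UACR and "Renal tube function" are marked at V0, V1, V3 and V4. Each of these measures is therefore taken twice before study drug, one week apart. Inflammatory mediators are marked from V1 only, so they have no such pair.

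Section 2.11 places the eGFR outcome "to evaluate the kidney function before and after the intervention on visit 1 to 4". The Abstract names the change in eGFR as primary and lists changes in several urinary markers as secondary. Section 2.5 likewise bases the sample size on "the primary outcome that is an alteration in baseline estimated glomerular filtration rate (eGFR").

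V0 has its own job. Section 2.6 says "Potential participants will be screened for eligibility a week anterior to study randomization", and eGFR (2.8.2), serum uric acid (2.8.1) and 24-h proteinuria (Table 1) all carry eligibility limits.

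**The concern.** When the outcome is change from baseline, the biological and assay error in the baseline sample enters each patient's change in full. Visits 1 to 4 include only one pre-dose eGFR, so that error is not averaged down, although another pre-dose eGFR from a week earlier will already be on file. In a single-centre trial of 118 patients, precision that needs no further visit or sample is worth taking. What is at stake is the width of the confidence interval for the primary outcome, and possibly for the renal secondary outcomes. The validity of the comparison is not in question.

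**Working it through.** **The plan's own figure.** Inputs from section 2.5: difference 10, SD 18.1, type 1 risk 5% (taken as two-sided), power 80%. The normal approximation gives 2 × (1.960 + 0.842)² × (18.1/10)² = 51.4, so 52 per group. The exact two-sample t-test gives 52.4, so 53, with 80.4% power at 53. Then 53/0.9 = 58.9, so 59 per group and 118 in total. The stated size reproduces. It uses the raw SD of 18.1 with no baseline term, so the choice of baseline does not move it.

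**Model for the gain.** Let T be the SD of true change to week 24, w the within-person SD of one measurement, and b the SD of true baseline between patients. Errors are independent across visits.
- Change score, V1 only: T² + 2w².
- Change score, mean of V0 and V1: T² + 1.5w².
- Baseline-adjusted, V1 only: b² + T² + w² − b⁴/(b² + w²).
- Baseline-adjusted, mean of V0 and V1: b² + T² + w² − b⁴/(b² + w²/2).

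The documents give none of T, w or b, so every value below is an assumption. For eGFR, b = 13 is about the SD of an even spread over the 15 to 60 eligibility window (45/√12 = 13.0).

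| Measure | T | w | Change variance, one → mean of two | Cut | Baseline-adjusted cut |
|---|---|---|---|---|---|
| eGFR (b = 13) | 6 | 2 | 44 → 42 | 4.5% | 4.4% |
| eGFR (b = 13) | 6 | 3 | 54 → 49.5 | 8.3% | 7.8% |
| eGFR (b = 13) | 6 | 3.5 | 60.5 → 54.4 | 10.1% | 9.2% |
| log UACR (b = 1.0 to 1.2) | 0.4 | 0.3 | 0.340 → 0.295 | 13.2% | 11.9 to 12.3% |
| log UACR (b = 1.0 to 1.2) | 0.4 | 0.45 | 0.565 → 0.464 | 17.9% | 14.4 to 15.4% |

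**What the cuts mean.** Interval width scales with the square root of variance. For eGFR change, √(42/44) = 0.977 and √(54.4/60.5) = 0.948, so the interval narrows by 2.3 to 5.2%. For log UACR, 0.340/0.295 = 1.15 and 0.565/0.464 = 1.22, so the gain equals about 15 to 22% more patients for that outcome.

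**Sensitivity.**
- Correlated errors: if V0 and V1 errors correlate at ρ, the change-score cut is multiplied by (1 − ρ). At ρ = 0.5 it halves, to about 2.3 to 5.1% for eGFR and 6.6 to 9.0% for log UACR.
- Ceiling: with T = 0 (all visits equally correlated), 2w² becomes 1.5w², a 25% cut.
- Correlation form: write r01 for the V0–V1 correlation and r for that of each with V4. The change variance is 2(1 − r) with one value and 1 + (1 + r01)/2 − 2r with the mean. Five assumed pairs with r01 of 0.8 to 0.95 and r of 0.6 to 0.9 give cuts of about 6 to 13% for change scores and 5 to 11% for adjusted analyses.
- Larger change SD: section 2.5 attaches 18.1 to eGFR values. If it were the SD of the change itself, the cut would be 0.5w²/18.1², which is 0.6% at w = 2 and 1.9% at w = 3.5.
- No baseline used: a comparison of week-24 values alone gains nothing.

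**The case against.** The strongest reply is that nothing here is wrong. A single value at the randomization visit is an accepted baseline, it contradicts no other text, and section 2.15 leaves detailed rules to a later analysis plan that could still use V0. That stands as far as validity goes. It does not dispose of the point, because section 2.11 itself names the visits that carry the primary outcome, and a plan that averaged V0 in would depart from that wording.

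A second reply is that section 2.15 lists t-tests, rank tests and repeated measures ANOVA without saying how baseline enters, so the gain could be zero. It could, but a week-24-only comparison would not match the change outcome named in the Abstract.

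A third is that V0 may be the qualifying value. Averaging it in would then add regression to the mean to within-group changes, which matters for the before-and-after description in 2.11. This is correct and should be acknowledged. Both arms are affected alike, so the between-arm comparison is untouched.

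Three stronger readings are tempting and not supported. A reader might infer that the V0 values are thrown away; the documents do not say so, and V0 can serve eligibility. A reader might infer that V1 alone is fixed as baseline for every marker; the visit 1 to 4 wording covers eGFR only, and section 2.12 names no visits. A reader might infer that these markers are stated to vary widely from day to day; the documents give no such statement or figure.

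**Conclusion.** The point holds as an optional improvement, not as an error. The protocol ties the primary eGFR outcome to visits whose only pre-dose value is V1, while its own schedule provides another. Using both would probably cut the variance of eGFR change by a single-digit percentage, up to about 10%, and would help log UACR somewhat more. These sizes rest on assumed SDs, on independent errors one week apart, and on an analysis that uses change from baseline or baseline adjustment. There is no bias between arms under either definition. For UACR, 24-h urine and tubular markers, the single-value baseline is a reasonable inference from section 2.10 and Table 3, not a stated rule.

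**What to change.** Add one sentence to sections 2.10/2.11, settled before unblinding. It should say that baseline for eGFR, and likewise for the renal secondary measures taken at both visits, is the mean of the V0 and V1 values, using the geometric mean for skewed urinary markers and V1 alone where V0 is missing. Apply this definition wherever a baseline or a change from baseline enters. Add a short note that, because V0 may be the value that qualified the patient, within-group before-and-after changes should be read with regression to the mean in mind. The cost is the wording only: no visit, sample or patient is added, and the sample size stays as stated.

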### Secondary outcomes

2.12

1Biological indicators: Serum creatinine (Scr), serum uric acid (SUA), blood urea nitrogen (BUN), serum nitric oxide (NO), xanthine oxidase (XOD), 24 h proteinuria, 24 h urine uric acid, urine microalbumin to creatinine ratio (ACR), urinary β2 microglobulin (β2-MG), urinary *N*-acetyl-β-D glucosaminidase (NAG), and urinary retinol-binding protein (RBP) levels will be tested in the clinical laboratory.2Inflammatory mediators: Blood plasma levels of interleukin 1β (IL-1β), interleukin 18 (IL-18), and monocyte chemoattractant protein 1 (MCP-1) will be measured as they are indicative of systemic inflammation, whereas the protein and mRNA expression levels of NLRP3 and Caspase-1 will be measured to assess the inflammatory characteristics of peripheral blood mononuclear cells (PBMCs). Plasma and serum samples will be stored at - 80 °C.3The scores for the curative effect associated with TCM syndromes.

### Measurement scale for TCM symptoms

2.13

We will apply the measurement scale for TCM symptoms based on the Guidelines for Clinical Research of Chinese Medicine (New Drug) [17], and score a value of 0, 1, 2, or 3 for each symptom indispensable to the diagnosis of the obstruction of phlegm turbidity and blood stasis syndrome, to sum up to yield a total score for each patient. Any change in this score will be formulated an efficacy indicator (EI), which will be used to assess the treatment efficacy:EI = (Total symptom score at baseline - Total symptom score post-treatment)/Total symptom score at baseline × 100%

The extent of enhancement in symptoms is to be revealed in four categories: full recovery (EI ≥ 90%), marked recovery (90% > EI ≥ 70%), moderate recovery (70% > EI ≥ 30%), and ineffective therapy (EI < 30%).

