#### Diagnostic criteria for TCM syndrome differentiation

2.8.3

Based on an evaluation of the diagnosis, syndrome differentiation, and curative effect in patients with hyperuricemic nephropathy (trial Scheme) [10], a patient, to be diagnosed with the obstruction of phlegm turbidity and blood stasis syndrome, has to perform no less than three of the primary symptoms listed below.

Primary symptoms.◆Pain or swelling in the joints◆Joint stiffness and deformation, possibly with subcutaneous gout nodules◆Impaired flexion and extension of joints◆Fatigue and swelling limbs◆Sticky and greasy in the mouth◆Increased nocturia◆Frequent urination◆Waist sinking and pain◆A red or dark tongue with ecchymosis◆A yellow and greasy coating of the tongue◆A string-like and slippery pulse

Inclusion criteria and exclusion criteria are listed below (Table 1).

**Table 1 tbl1:** Eligibility criteria for the trial.

Inclusion criteria
To be eligible for participation patients must be:
◆ Individuals diagnosed with hyperuricemic nephropathy beyond three months as listed above, at the same time diagnosed with obstruction of phlegm turbidity and blood stasis syndrome in TCM
◆ Aged between 18 and 75 years
◆ The eGFR value ≥ 15 mL/min/1.73 m^2^ and <60 mL/min/1.73 m^2^
◆ Should be able to provide serum or urine pregnancy test results (for females), 24 h earlier than JNSF administration
◆ Should be able to provide the investigators with informed consent in written form for trial enrollment

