### Statistical analysis

2.15

The independent statisticians will formulate a formal and detailed plan for statistical analysis prior to locking the database. Comparing the baseline demographic data of each group will use with a χ^2^ test or Student's t-test. The means ± standard deviations or medians will express continuous variables, and an independent *t*-test or the Wilcoxon rank sum test will be used to analyze differences of such variables. Repeated measures ANOVA will be built for these outcomes. The numbers and percentages will express categorical variables, and the Fisher exact test or the Mann-Whitney *U* test will be used to calculate and compare differences in such variables respectively. The missing data will be handled with multiple imputation. According to the intention-to-treat principle, all patients enrolled will be embraced in the primary analysis. An independent statistician will use SPSS 24.0 to perform the statistical analysis. Calculations will be performed using GraphPad Prism 6.01 software.

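### The TCM efficacy indicator is a percent change from the patient's own baseline in four classes: equal point changes get different verdicts, worsening is not separated, and no baseline-adjusted score analysis is committed to

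*Protocol article*

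**What the plan says.** Section 2.13 asks investigators to "score a value of 0, 1, 2, or 3 for each symptom indispensable to the diagnosis" and to sum the items. The total becomes an efficacy indicator, "EI = (Total symptom score at baseline - Total symptom score post-treatment)/Total symptom score at baseline × 100" (a percentage), and the section gives its role: "Any change in this score will be formulated an efficacy indicator (EI), which will be used to assess the treatment efficacy". It then adds: "The extent of enhancement in symptoms is to be revealed in four categories". These are full (at least 90%), marked (70 to below 90%), moderate (30 to below 70%) and ineffective (below 30%). The ineffective class has no lower bound.

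Section 2.8.3 lists 11 primary symptoms, and a patient "has to perform no less than three of the primary symptoms listed below" to qualify. Table 3 schedules TCM symptoms at every visit from screening to week 24.

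Section 2.12 lists the secondary outcome as scores for TCM curative effect. Section 2.15 gives generic methods: a t-test or rank sum test for continuous variables, repeated measures ANOVA for outcomes it does not name, and for categorical variables "the Fisher exact test or the Mann-Whitney *U* test will be used to calculate and compare differences in such variables respectively". It does not say which of these applies to the TCM outcome. It names no method with the baseline value as covariate.

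**The concern.** Section 2.13 is the only text that says how TCM efficacy is judged, and it names the EI. A percent change divides by a baseline that may be small, so the class a patient lands in depends on the starting score as well as on how far the score moved. The open-ended lowest class gives a patient who deteriorates the same label as one who improves slightly. If the four classes are also what is tested between groups, a score with many possible values is reduced to four, and the baseline enters only through the ratio.

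The other efficacy outcomes in sections 2.11 and 2.12 are laboratory measures, so this is the trial's only symptom-based evidence of efficacy. At stake are the interpretability and the power of that one secondary result.

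**Working it through.** **The plan's own figure.** The only stated calculation concerns eGFR (section 2.5): difference 10, SD 18.1, 5% two-sided, 80% power. The normal approximation gives 2 × (1.96 + 0.84)² × (18.1/10)² ≈ 51.4, so 52 per group. The t-test version gives 52.4, so 53. With 10% drop-out, 53/0.9 = 58.9, so 59 per group and 118 in total. This reproduces. No figure is stated for the TCM outcome.

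**Step 1: dependence on baseline.** Inputs: items scored 0 to 3; 11 symptoms, so a maximum of 33 if all are scored; at least three symptoms present, so a minimum of 3 if each scores 1. EI = (baseline − post)/baseline.

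| Baseline | EI of a 3-point fall | Class | Points needed for *moderate* |
|---|---|---|---|
| 3 | 3/3 = 100% | full | 1 |
| 6 | 3/6 = 50% | moderate | 2 |
| 10 | 3/10 = 30% | moderate | 3 |
| 11 | 3/11 = 27.3% | ineffective | 4 |
| 15 | 3/15 = 20% | ineffective | 5 |
| 33 | 3/33 = 9.1% | ineffective | 10 |

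A one-point fall from 3 (33.3%) is *moderate*, while a four-point fall from 15 (26.7%) is *ineffective*. From 3, *marked* cannot be reached: two points is 66.7% and three is 100%.

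**Step 2: pooling.** From a baseline of 11, post-treatment totals of 8 (EI 27.3%), 11 (0%) and 14 (−27.3%) all fall in the lowest class. In nine simulated scenarios (assumed baseline means 12 to 20, SDs 4 to 5), between 16% and 46% of that class had worsened.

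**Step 3: cost if the four classes are tested.** The documents give no mean, SD, correlation or class shares for the TCM score, so everything here is assumed. Relative efficiency is [(1.96 + z of power, classes)/(1.96 + z of power, ANCOVA)]².

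- *Nine scenarios, 53 per arm, 4,000 runs each.* Mann-Whitney on the classes against ANCOVA on the total: 0.41 to 0.74, a loss of 26 to 59%; seven of the nine lost less than 40%. Example (baseline mean 15, SD 4, 55% in the lowest class): power 0.511 against 0.698, so (1.99/2.48)² ≈ 0.64. The extreme (0.41) had 79% of patients in the lowest class.
- *Other settings, 53 per arm.* The loss was 14 to 37% under an additive effect and about 0 to 20% when treatment acts in proportion to baseline.

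**Step 4: what the loss consists of.**

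- *Missing adjustment.* With an additive 0.5 SD effect, baseline mean/SD of 9/4, 12/4 and 15/5, correlation 0.5 and a 25% mean fall in controls, the classes had relative efficiency 0.71 to 0.78 against ANCOVA but 0.95 to 1.00 against an unadjusted t-test on the week-24 total. This agrees with theory: an unadjusted test keeps about 1 − 0.5² = 0.75 of ANCOVA's efficiency. In those settings nearly all of the loss is the missing adjustment.
- *The cut.* Under proportional odds, four classes with shares p keep 1 − Σp³ of the information. Equal shares: 1 − 4 × 0.25³ = 0.94, a 6% loss. Shares of 40/45/12/3%: 16%. Shares of 60/30/8/2%: 24%. Shares of 80/17/2/1%: 52%. The cut is costly mainly when most patients fall in one class.

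**The case against.** The strongest reply is that the article never says the four classes are the tested outcome. The EI itself is a continuous percentage, and the sentence on classes can be read as reporting language. Section 2.12 speaks of scores, section 2.15 supplies continuous tests, and a detailed analysis plan is to follow before database lock. This stands. A reader might infer that the plan tests only the classes or rules out analysing the total, and the documents do not support that. What remains is that section 2.13 positively names the EI as the efficacy measure, no passage commits to a baseline-adjusted comparison of the total, and even a continuous EI keeps the dependence on baseline.

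A baseline of 3 is a corner case; under assumed baselines about 1 to 8% of patients would have it. That is fair, but the change of verdict between 10 and 11 lies inside the usual range and does not need the corner.

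Deterioration is also not lost from the record. Totals are collected at each visit and adverse events from week 4. The pooling affects the EI summary only.

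Finally, section 2.13 bases the scale on a cited guideline that is not available here. That is a reason to keep the classes, not to rest the between-group comparison on them.

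**Conclusion.** The dependence on baseline and the pooling of worsening are certain: they follow from the EI formula and its cut-points, granted only that each qualifying symptom scores at least 1.

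The cost in power is conditional. It arises only if the classes are tested, and it is then roughly 0 to 40% against a baseline-adjusted analysis of the total in most assumed settings, with 59% at the extreme. It is smallest if treatment acts in proportion to baseline, and part of it is absent adjustment rather than categorisation. Two stronger statements should be avoided. A fixed loss of a quarter or more is not a property of the plan, since the documents give no score distribution and some plausible settings show almost no loss. Losses computed for a two-way split at 30% do not apply, because no such split is proposed.

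This is a worthwhile correction to one secondary outcome. It does not touch the eGFR sample size or the primary conclusion.

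**What to change.** State in sections 2.13 and 2.15, and carry into the analysis plan before database lock, that the between-group TCM analysis compares the week-24 total score by ANCOVA with the baseline total as covariate, or by a mixed model over weeks 4, 12 and 24 (visits V2 to V4) with the same covariate. Keep the four guideline EI classes as a descriptive table and show patients with EI below 0 on their own line.

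The cost is wording only, since the scores are already scheduled at every visit. ANCOVA was at least about as efficient as the test on the classes in every setting examined. The one downside is that the headline TCM result becomes less directly comparable with trials that test the guideline classes; the descriptive table largely meets this.
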